## Efficacy evaluations

From week 0 to week 16, researchers will utilize MADRS scores as a primary outcome to assess changes in depressive symptoms. A total score of 0–60 is obtained by completing 10 items with scores ranging from 0 to 6[40]. The depressive symptoms will be grouped as extreme, major, moderate, or mild according to the following scores: MADRS > 35, 30 ≤ MADRS < 35, 22 ≤ MADRS < 30, 12 ≤ MADRS < 22, respectively, and MADRS < 12 indicates no depressive symptoms. Compared with the baseline, a MADRS total score reduction of 50% will be defined as a significant antidepressant response, while a reduction of 20% will be defined as an improvement.

Secondary outcome measures include: (1) Self-rated depressive symptoms on the Baker Depression Scale, second Chinese version (BDI-II-C): This scale has high internal consistency, and reflects the severity of depression in the past two weeks. It contains 21 items, each rated on a 0–3 scale, with an overall score of 0–63 points. The levels of depression will be grouped as severe, moderate, or mild according to the following ranges of scores: 29–63, 20–28, and 14–19, respectively, and a score of 0–13 will be classified as no depression[41]. (2) Behavioral Activation for Depression Scale Short Form (BADS-SF): This scale consists of nine items that measure changes in behavioral activation during the past week, including the measurement day. The activation (AC) subscale includes questions 1, 2, 3, 4, 5, and 9, while the avoidance (AV) subscale includes questions 6, 7, and 8. The scale uses a 7-level scoring method, which ranges from 0 (not at all) to 6 (completely). A higher score for an item represents an answer that is closer to the item statement. The scale has been demonstrated to have robust reliability and validity[42] (3) Adolescent Non-suicidal Self-injury Assessment Questionnaire (ANSAQ): This questionnaire is divided into two parts: a behavioral questionnaire (12 items) and a functional questionnaire (19 items) to evaluate self-injury behavior[43]. It uses the Likert 5-point scale, where “1 to 5” corresponds with “no, occasionally, sometimes, often, always”, respectively. A higher score represents a more serious degree of self-injury. The questionnaire has high internal consistency, while that of the behavioral questionnaire was 0.921. In this study, we will only use the behavioral dimension of the questionnaire (12 questions in total) to assess whether the depressed adolescents engage in self-injury behavior. (4) Insomnia Severity Index (ISI): this is used to evaluate the severity of insomnia in patients. Total scores of 0–28 are obtained according to responses to 7 items with scores ranging from 0 to 4[44]. According to the scoring guide, scores for mild, moderate, and severe clinical insomnia range from 8–14, 15–21, and 22–28, respectively, while scores less than 7 are considered to represent non-clinical insomnia. (5) International Physical Activity Questionnaire-Short Forms (IPAQ-SF): This short form records activity for four intensity levels: 1) vigorous-intensity activity such as aerobics, 2) moderate-intensity activity such as leisure cycling, 3) walking, and 4) sitting[45]. These four intensity levels (except sitting) can be determined and reported as MET-minutes per week. The IPAQ-SF has good internal consistency. (6) Custom 5-point Likert score acceptance questionnaire: to assess the acceptance of the intervention by participants and their families.

At the baseline, week 2 (the end of the basic intervention), week 4 (the end of all the high-order intervention), week 8, and week 16, participants from the two groups will be evaluated with the corresponding scales to assess the degree of depression, behavioral activation level, non-suicidal self-injury behavior, and sleep quality scores. We will also calculate the improvement of symptoms for each dimension in each group at each time point, and then compare the divergences between the two groups. All participants will receive an electronic exercise wristband as a reward after they completed the follow-up.

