Participants aged 12 to 17 years will be eligible if they are defined as having depression by using DSM-5, but if they meet one of the following exclusion criteria they will not be allowed to take part: (1) Participants with a DSM-5 diagnosis of other mental disorders, including addictive disorders, developmental disorders, bipolar disorder, substance-related disorders, and schizophrenia (except anxiety disorders); (2) Participants with severely disruptive or aggressive behaviors, or positive suicidal ideation (suicide item scores of the MADRS > 4); (3) Participants with severe psychotic symptoms (presence of pain or common hallucinations and/or delusions); (4) Participants with clinically significant and uncontrolled pulmonary, endocrine, immunological, cardiovascular diseases (based on ancillary examination, physical examination, medical history); (5) According to the research group, participants who could not cooperate with the cognitive function tests or would not be suitable for this study.

Prior to participation in this study, all subjects and their legal guardians must be fully informed about the project and sign a written informed consent form. The participants will be divided into intervention group and control group according to a pre-defined randomization protocol. The intervention and control groups received 4 weeks of BAPT and 4 weeks of BA respectively. Participants in both groups will be treated and cared for according to the same criteria, but will not be involved in any other psychological therapy programs.

Therapeutic effect evaluation will be done at the baseline, week 2 (the end of the basic intervention), week 4 (the end of all the high-order intervention), week 8, and week 16 by the MADRS, BDI-II-C, BADS-SF, ANSAQ, ISI, IPAQ-SF, and Likert Scale. The primary outcome was whether BAPT could decrease depressive symptoms in adolescents by MADRS scores.

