## Hypotheses

Primary: BAPT (intervention group) will be more effective than BA (control group) in relieving depressive symptoms and enhancing treatment adherence in adolescents with depression.

Secondary: BAPT (intervention group) will be more effective than BA (control group) in increasing levels of physical activity, reducing non-suicidal self-injury behavior, and ameliorating sleep quality.

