### Fig. 1 Study period

[figure not shown]

**Abbreviations:** ***BMI***: Body Mass Index; ***MADRS***: Montomery-Asberg Depression Rating Scale; ***BDI-Ⅱ-C***: Beck Depression Inventory-China; ***BADS-SF***: Behavioral Activation for Depression Scale Short Form; ***ANSAQ***: Adolescent Non-suicidal Self-injury Assessment Questionnaire; ***ISI***: Insomnia Severity Index; ***IPAQ-SF***: International Physical Activity Scale Short Form; ***Physical activity intensity***: collecting data regarding calorie consumption (kcal) and metabolic equivalents; ***Likert Scale***: assessing the acceptance of the intervention by patients and their families.

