### Fig. 2 Research flow chart

[figure not shown]

*****Participant data regarding physical intensity were collected every week during the study.

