## Blinding

This study will use a single-blind approach because in this intervention, the participants and health care professionals cannot be blinded to the study conditions. Therefore, to minimize the impact of information bias, the researcher administering the outcome measurement will be unaware of the group assignment. To maintain researcher blindness regarding group assignment, the same researcher will not conduct follow-up measurements on the same pair of elements.

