## Intervention

All interventions will be conducted in a group format and delivered by experienced psychotherapists. All participants will use electronic exercise wristbands (Beijing Xiaomi Technology Co., LTD., [Product number](javascript:;): Xiaomi Band 7pro, M2140B1) to record the daily intensity of their physical activities. The electronic exercise wristbands utilize photocapacitance pulse wave tracing (PPG) and acceleration sensors to measure the intensity of physical activity in adolescents[34-37]. During the study period, the participants will only receive conventional clinical medication and care, and will not be involved in any other psychological therapy programs.

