## Physical activity intensity

The Metabolic Equivalent (MET) can be used to express the relative energy metabolism level of physical activity. Depending on the intensity of the exercise, which can be divided into light, medium, or heavy grade, it can be represented by a score of 0–3, 3–6, and more than 6, respectively.

The researchers will collect data regarding the participants' physical activity intensity once a week. Participants who complete the homework and exercise at a moderate intensity for 150 minutes or above per week will be rewarded with small gifts for activation and positive reinforcement. The electronic exercise wristbands will be purchased and distributed by the project team to ensure monitoring consistency.

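### The physical-activity hypothesis is assigned only to the self-reported IPAQ-SF in unblinded participants, while the wristband data collected weekly in both arms have no stated outcome role

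*Protocol*

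**What the plan says.** - **Hypothesis.** The protocol's Hypotheses section states, as the first part of the secondary hypothesis, that "BAPT (intervention group) will be more effective than BA (control group) in increasing levels of physical activity".
- **Outcome lists.** Under Efficacy evaluations, the fifth of six secondary outcomes reads "5) International Physical Activity Questionnaire-Short Forms (IPAQ-SF): This short form records activity for four intensity levels". It is the only activity measure in that list. The Synopsis says that effect will be evaluated at baseline and weeks 2, 4, 8 and 16 "by the MADRS, BDI-II-C, BADS-SF, ANSAQ, ISI, IPAQ-SF, and Likert Scale". The wristband is not named there.
- **Blinding.** The Blinding section says that "the participants and health care professionals cannot be blinded to the study conditions". Its remedy is that the researcher administering the measures does not know the allocation.
- **Difference between arms.** Each BAPT session includes 30 minutes of gamified activity, and BAPT homework suggests socio-motor games (Intervention group: BAPT). The control arm has neither (Control group: BA).
- **Device.** All participants wear a wristband "to record the daily intensity of their physical activities" (Intervention). The key to Fig. 1 describes physical activity intensity as "collecting data regarding calorie consumption (kcal) and metabolic equivalents". The section Physical activity intensity says "The researchers will collect data regarding the participants' physical activity intensity once a week", and the note to Fig. 2 says "Participant data regarding physical intensity were collected every week during the study".
- **Use of the device data.** The only apparent use is a small gift for participants who do their homework and reach 150 minutes of moderate exercise in a week. Data analysis does not mention the device.

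**The concern.** A blinded assessor protects a rating that the assessor makes. It does not protect a recall score that the participant supplies. For this outcome the participant is the source of the data, knows the allocation and, in the BAPT arm only, has been taught that active play is part of the treatment. Differential reporting is plausible, and it need not stop when the sessions stop.

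At stake is the reading of a named secondary objective. If the arms differ on IPAQ-SF, the protocol as written has no designated measure that could separate more activity from more reported activity. Yet a measure that does not depend on recall is already being collected in the same participants.

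**Working it through.** **1. Which measure answers the hypothesis?** The Hypotheses section names no instrument. The Synopsis and the secondary outcome list each contain one activity measure, the IPAQ-SF. The assignment therefore follows from the two lists rather than from the hypothesis itself.

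**2. What differs between arms that could shift self-report?**

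| Feature | BAPT | BA |
|---|---|---|
| Knows allocation | yes | yes |
| Active games in sessions | yes | no |
| Socio-motor games suggested in homework | yes | no |
| Wristband | yes | yes |
| Gift for 150 minutes plus homework | yes | yes (no restriction by arm is stated) |

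Only the two game rows differ. The case for differential reporting rests on these, not on the gift.

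**3. How large could the effect be?** The protocol gives no figure for physical activity and none for reporting bias. Its only design figure is 84 per arm for the depression score. Reading the stated 90% confidence interval as 90% power, that figure reproduces:

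- n = 2 × (1.960 + 1.282)² × (9.5 / 4.8)² = 82.3, so 83 per arm; the t-based solution is 83.3, so 84.

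This does not bear on physical activity and serves only as the number analysed below.

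Illustration, with bias b assumed: no true difference, two-sided 5% test, and a shift of b standard deviations in favour of BAPT. The chance of a significant result for BAPT is

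- P = 1 − Φ(1.96 − b × √(n/2))

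For b = 0.2 and n = 84: 0.2 × √42 = 1.296; 1.96 − 1.296 = 0.664; P = 0.253.

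| Assumed b (SD) | 84 per arm | 100 per arm |
|---|---|---|
| 0 | 2.5% | 2.5% |
| 0.1 | 9.5% | 10.5% |
| 0.2 | 25.3% | 29.3% |
| 0.3 | 49.4% | 56.4% |

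A larger sample makes the problem worse, because bias does not shrink with n.

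**4. What could the device supply?** Sessions end at week 4. If collection runs to week 16, there are up to 16 − 4 = 12 weekly device readings after treatment, against two questionnaire readings (weeks 8 and 16). Twelve is an upper bound, since wear to week 16 rests on the note to Fig. 2.

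**5. Would the device be neutral during treatment?** No. Nine BAPT sessions with 30 minutes of games give 9 × 30 = 270 minutes over four weeks, or 67.5 minutes a week. The protocol rates these games as moderate to high intensity. The band would record them in one arm only, so session time must be excluded or the comparison placed after week 4.

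**The case against.** Several points on the other side are sound.

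- **The device data may be analysed after all.** A reader might infer that they go unused. The documents do not establish that. The secondary list is introduced as what the outcomes include, the key to Fig. 1 sets physical activity intensity beside the other measures, and the figure is not shown. A statistical analysis plan may exist. What stands is narrower: no outcome role is stated. If the open wording does admit the device, two measures could answer one hypothesis with neither named as deciding. Which measure answers a stated hypothesis is an outcome definition and belongs in the protocol.
- **The incentive is common to both arms.** A reader might infer that BAPT participants alone are rewarded for being active. The text does not say so; the gift has no restriction by arm.
- **The wristband has its own biases.** Wear is controlled by the same unblinded participants, so non-wear may differ by arm. Minutes at moderate intensity are close to the quantity that earns the gift. No section says that the band is worn before treatment, whereas IPAQ-SF has a scheduled baseline. Efficacy evaluations also describes a wristband given as a reward after follow-up, which leaves the wear arrangement unclear. All of this stands, and it rules out any claim that the bias can be removed at no cost.
- **Other secondary outcomes are questionnaires too.** This is true of the BDI-II-C, for example. But physical activity is the one for which a device measure is already collected in everyone.

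**Conclusion.** The point holds in a limited form. The outcome lists assign the physical-activity hypothesis to self-report in unblinded participants, only one arm receives active games and game homework, and the weekly device data have no stated outcome role. A between-arm IPAQ-SF difference could partly reflect differential reporting.

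The size is unknown. The false-finding rates of about 10%, 25% and 49% at 84 per arm depend entirely on assumed shifts of 0.1, 0.2 and 0.3 SD and on no true difference. They show sensitivity and do not estimate the bias. A reader might infer that any observed difference would be wholly artefact; nothing in the documents supports that. Nor is there a wider threat to the trial: the outcome is secondary, and the primary MADRS result and the sample size are unaffected. The change is worth making, but it is not critical.

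**What to change.** Under Efficacy evaluations, add wristband-recorded weekly activity as the main measure for the physical-activity hypothesis:

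- Define the variable, for example MET-minutes per week or weekly minutes at 3 MET or more (the lower bound of the protocol's own medium grade).
- Compare the arms in stated weeks after the sessions end, or exclude session time.
- Set a minimum wear time for a week to count, and report wear time by arm.
- State in which weeks the band is worn, including whether it is worn before treatment starts.
- Keep IPAQ-SF, with its scheduled baseline, as supportive.

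No new device or collection round is needed if weekly collection continues into the weeks chosen. The cost is the outcome wording, a wear-time rule and the data handling that follows.

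Three drawbacks remain. Non-wear will leave missing data that may differ by arm. Recorded activity may be influenced by the gift in both arms. Without an assured pre-treatment device baseline, the comparison rests on randomisation at follow-up.

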## Demographic and clinical data

Demographic data (age, sex, occupation, culture, residence, family structure, economic income, etc.), medical expenses, growth history, history of tobacco, alcohol and other psychoactive substance use, psychiatric symptoms, and length of hospital stay will be collected during the screening stage. All participants and their families will volunteer to participate and sign informed consent.

## Auxiliary inspection:

Electrocardiograms, routine blood analysis, and biochemical indexes of clinical treatment will be completed at the baseline assessment.

## Physical activity intensity

The Metabolic Equivalent (MET) can be used to express the relative energy metabolism level of physical activity. Depending on the intensity of the exercise, which can be divided into light, medium, or heavy grade, it can be represented by a score of 0–3, 3–6, and more than 6, respectively.

The researchers will collect data regarding the participants' physical activity intensity once a week. Participants who complete the homework and exercise at a moderate intensity for 150 minutes or above per week will be rewarded with small gifts for activation and positive reinforcement. The electronic exercise wristbands will be purchased and distributed by the project team to ensure monitoring consistency.

## Data management

The Case Report Form (CRF) will be utilized to document the demographic information and clinical symptoms of all participants, which will subsequently be stored in the database through a process of double data entry. The primary responsibility of the study leader will be to ensure the integrity, accuracy, and promptness of the data inputting process. In an effort not to disclose the privacy of participants, researchers will remove the names, phone numbers, and addresses that are not related to the study. Numbers will be used to identify the participants. In addition, the original CRF will be securely stored throughout the study and will be accessible to the project leader. A dedicated physician ([name]) will monitor the wholeness, uniformity and plausibility of the data.

## Statistical analysis

### Sample size calculation

The depressive symptom scores of the study subjects will be used as the main outcome index, with a bilateral α = 0.05 and a 90% confidence interval. In a previous study on the effects of BA combined with traditional exercise therapy, the depression scores of the intervention group at the baseline and at the 16-week follow-up period were 27.3 ± 8.0 and 16.0 ± 9.5, respectively[46]. Therefore, we expect that the depression score of the experimental group in the present study could be decreased by 11.3 points compared with the baseline and 4.8 points compared with the control group. We used PASS 15 software to calculate the sample size of the experimental group: N1 = N2 = 84. Considering the expectation that 10%­–20% of the cases will be

lost during the period following the study, the number of participants needed in the intervention group and control group will be about 100, respectively.

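### The sample-size statement gives a 90% confidence interval where 84 per arm implies 90% power, and 100 per arm keeps 84 evaluable only up to 16% loss, short of the stated 20%

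*Protocol*

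**What the plan says.** Everything on this point is in the protocol's Sample size calculation section. The depression score is the main outcome, and the error rates are set "with a bilateral α = 0.05 and a 90% confidence interval". The section then cites an earlier study of behavioral activation (BA) combined with exercise. Its intervention group scored "27.3 ± 8.0 and 16.0 ± 9.5, respectively" "at the baseline and at the 16-week follow-up period". From this the protocol expects the experimental group to fall by "11.3 points compared with the baseline and 4.8 points compared with the control group". PASS 15 is reported to give 84 per arm. With loss expected to lie between 10% and 20%, the section concludes that "the number of participants needed in the intervention group and control group will be about 100, respectively".

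The section does not name a power or say which SD went into the software. The Data analysis section confirms the 0.05 significance threshold. It plans an intention-to-treat analysis with a mixed-effect regression of group and time.

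**The concern.** There are three separate problems.

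- **The 90% figure.** A sample size for comparing two means needs α, power, a difference and an SD. The statement supplies α, then a confidence level where the power should be. The two do not agree with each other either, since a two-sided α of 0.05 corresponds to a 95% interval. As written, a reader cannot tell what power the trial was designed for, and cannot reproduce 84 without guessing both the power and the SD.
- **The allowance for loss.** The section names an upper bound of 20%, but the enrolment figure does not preserve 84 evaluable participants per arm at that bound.
- **The 4.8 points.** This difference is presented as following from the cited values. Those values are one group's scores before and after treatment, so they yield the within-group change of 11.3 and nothing about a control group.

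The sample-size basis is normally carried into the trial report, so an uncorrected statement would be repeated there.

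**Working it through.** **Inputs from the protocol.** Two-sided α = 0.05; between-arm difference 4.8; cited SDs 8.0 (baseline) and 9.5 (16 weeks); 1:1 allocation; 84 per arm before loss; loss 10% to 20%; about 100 per arm enrolled.

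**Step 1. Reproduce 84.** Read 90% as power and take SD = 9.5 in both arms.

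- Normal approximation: n = 2 × (1.960 + 1.282)² × 9.5² / 4.8² = 82.3, so 83 per arm.
- Two-sample t-test (noncentral t): n = 83.3, so 84 per arm, as stated. Power at 84 is 90.2%.

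**Step 2. Try other settings.** Difference 4.8, two-sided α 0.05, n per arm from the t-test:

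| SD | 80% power | 90% power | 95% power |
|---|---|---|---|
| 8.0 (baseline) | 45 | 60 | 74 |
| 8.75 (mean of 8.0 and 9.5) | 54 | 71 | 88 |
| 8.78 (8.0 and 9.5 pooled) | 54 | 72 | 88 |
| 8.85 (change score, correlation 0.5) | 55 | 73 | 90 |
| 9.5 (16 weeks) | 63 | **84** | 103 |
| 12.42 (change score, correlation 0) | 107 | 142 | 175 |

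The two change-score correlations are assumptions used only to widen the search. Working backwards, 84 per arm at 80% power would need an SD of 11.04, which the protocol does not give. At 90% power it allows an SD of up to 9.54, which fits 9.5.

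Taking the 90% interval literally, as two-sided α = 0.10, gives 68 per arm at 90% power and SD 9.5. Two settings at that α come near 84: 95% power with SD 9.5 (85 by the normal approximation), and 80% power with SD 12.42 (83). Both contradict the stated α of 0.05.

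**Step 3. Allowance for loss.** Enrolment needed = 84 / (1 − loss).

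- 10%: 84/0.90 = 93.3, so 94 per arm
- 15%: 84/0.85 = 98.8, so 99 per arm
- 16%: 84/0.84 = 100 per arm
- 20%: 84/0.80 = 105 per arm (210 in total, against 200)

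The shortcut of multiplying instead of dividing gives 84 × 1.20 = 100.8. Either that or a mid-range loss of 15% could explain the figure of about 100; the protocol does not say which.

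**Step 4. Consequence at 20% loss.** 100 × 0.80 = 80 per arm remain. With difference 4.8 and SD 9.5, an unadjusted t-test on those 80 per arm has 88.8% power, against 90.2% at 84. The difference is 1.4 percentage points.

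**Step 5. The 4.8 points.** 27.3 − 16.0 = 11.3, which matches the stated within-group change. No control-group value appears in the section, so 4.8 cannot be derived from what is quoted.

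**The case against.** The strongest reply is that nothing in the design is broken. The 84 reproduces exactly once 90% is read as power, so the error is a label and the intended meaning can be recovered. That is correct, and it rules out the stronger reading that the sample size was miscalculated. It does not make the statement right: it still names the wrong quantity and leaves the reader to infer the SD.

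On loss, the protocol gives a range and an approximate number, and 99 at 15% loss shows that about 100 suits the middle of that range. The section does not expressly promise 84 evaluable at the 20% extreme. In addition, 88.8% belongs to an unadjusted completer analysis. The planned mixed model can use earlier visits from participants lost later, and adjustment for baseline can add precision. As an illustration, suppose a baseline–outcome correlation of 0.3 to 0.5, which the documents do not give. The residual SD is then 9.5 × √(1 − 0.09) = 9.06 down to 9.5 × √(1 − 0.25) = 8.23, and power at 80 per arm is 91% to 96%. This stands, and it is why the shortfall is minor. The arithmetic at 20% still gives 105, and the protocol chose that upper bound itself.

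On the 4.8 points, a reader might infer that the difference is an unsupported assumption presented as evidence. The protocol does not establish that. The reference list titles the cited source as a randomized pilot trial of exercise added to brief BA, so it may contain a comparator value from which 4.8 was taken. All that can be said is that the derivation is not shown.

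A reader might also want power tabulated for smaller differences. The protocol marks no smaller difference as relevant, so its absence is not an error.

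**Conclusion.** The point holds as an error of statement with a minor shortfall attached. The phrase "a 90% confidence interval" is wrong beside a two-sided α of 0.05, and no power is stated. Among the two-sided 0.05 settings tried, 84 per arm corresponds only to 90% power with SD 9.5. That SD is an inference from the cited 16-week value, and the sponsor must confirm it.

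Enrolling 100 per arm preserves 84 evaluable up to 16% loss, not 20%. The worst case within the protocol's own range is about 89% power, assuming a 4.8-point difference, SD 9.5 in both arms, and an unadjusted t-test with no information from those lost. The source of "4.8 points compared with the control group" is not shown; whether it is an assumption or a derived value cannot be settled from the protocol. None of this calls the trial's size into question.

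**What to change.** In the Sample size calculation section:

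1. Replace the 90% confidence interval with 90% power, beside the two-sided α of 0.05.
2. State the SD used in PASS: 9.5, if the sponsor confirms it.
3. State that 100 per arm maintains 84 evaluable up to 16% loss, and that at 20% loss power is about 89% for an unadjusted completer t-test.
4. Show where the 4.8-point between-arm difference comes from. If the cited study supplies it, quote the control value; label it an assumption only if the study does not.

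No extra enrolment is needed. The cost is a few sentences, plus a check by the sponsor of the PASS inputs and the cited source. The only less favourable change is that the stated power at the top of the loss range becomes about 89%.
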